#### **11.2.1. Reporting of SAEs**

Life-threatening (grade 4 or 5) SAEs, deaths, and unknown reactions or unexpected events that occur in the course of any patient’s treatment of study (from the time of consent) or within 30 days following cessation of treatment are reportable. All SAE’s will be reported to the IRB. The initial report for each SAE or death should include at minimum the following information:

- Protocol # and title
- Patient initials, study identification number, sex, age
- Date the event occurred
- Description of SAE
- Description of patient’s condition
- Indication whether the patient remains of study
- Causality or causal relationship

De-identified source documentation (i.e. discharge notes) must be sent with the SAE Report Form. Follow-up information including severity, action taken, concomitant medications, and outcome should be communicated to Duke as soon as possible using the same forms mentioned above.

As soon as an investigator becomes aware of an AE that meets the definition of serious:

- DCI Safety Surveillance must be notified and they will submit to Pfizer of designee within 24 hours of Investigator's awareness, even if it is not felt to be drug related. Report to Pfizer U.S. Clinical Trial Department ([contact])
- The investigator agrees to provide supplementary information requested by Pfizer Drug Safety personnel or designee.

SAEs will be reported by the P.I. in an expedited manner to the Duke University Health System (DUHS) Institutional Review Board (IRB) office, NIDA, and FDA.

SAEs will be reported to the DUHS IRB using the following timelines:

- 24 hours – for an unanticipated study-related death
- 1 week (5 business days) – for an unanticipated problem that is a serious adverse event
- 2 weeks (10 business days) – for an unanticipated problem that does not meet the criteria of a serious adverse event

SAEs will be reported to the NIDA Serious Adverse Event Tracking and Reporting System (SAETRS) within 72 hours. The NIDA Program Official will be kept apprised of IRB actions related to SAEs and any plan to modify the protocol as a result of IRB recommendation will be subject to NIDA approval.

In accordance with applicable regulations, investigators will submit the SAE report to their local IRB according to local IRB institutional guidelines.

Duke as the lead center is responsible for reporting the serious adverse event to the FDA in accordance with 21 CFR 312.32. Any SAE that is possibly related and unexpected must be submitted to the FDA. This will be done by DCI Safety Desk and/or coordinate with study team regulatory coordinator.

- These reports are to be filed utilizing the Form FDA 3500 (MedWatch Form) completed by the DCI Safety Desk.
- The final MedWatch Form must be submitted by the study site to Pfizer within one to two business days of submission to the FDA to allow Pfizer time to cross-report to Pfizer IND.

### **11.3 Emergency Unblinding of Investigational Treatment**

Study staff in direct contact with participants (Clinical Trials Assistants, Study Clinician) will not be blinded to the selection of Varenicline or Nicotine Patch. All study staff in direct contact with participants will be blinded to the randomization to adaptive vs standard treatment algorithms. The Clinical Research Coordinator will have access to participant randomization for emergency un-blinding. In the case that Emergency un-blinding is required, the Principle Investigator will contact the Clinical Research Coordinator directly to obtain the necessary information. Emergency contact information for un-blinding will be the email and cell phone number of [name], the study CRC: [[contact]](mailto:[contact]); [contact].

### **11.4 Other Reportable Information**

Other reportable information including pregnancy, development of disease or hospitalization for non-study related causes will be reported as AEs or SAEs depending on the severity and assessed as to whether these are related to study procedures.

### **11.5 Special Warnings and Precautions**

There are no special warnings or precautions for this study.

### **11.6 Stopping Rules**

The study will be stopped prior to its completion if: (1) difficulty in study recruitment or retention will significantly impact the ability to evaluate the study endpoints; (2) any new information becomes available during the study that necessitates stopping the study; or (3) other situations occur that might warrant stopping the study. The P.I. will include an assessment of futility in the annual progress report to NIDA and will consult with the study monitors to assess the impact of significant data loss due to problems in recruitment, retention, or data.

### **11.7 Safety Oversight Committee (SOC)**

The SOC is responsible for annual data and safety monitoring of DUHS sponsor-investigator phase I and II, therapeutic interventional studies that do not have an independent Data Safety Monitoring Board (DSMB). The primary focus of the SOC is review of safety data, toxicities and new information that may affect subject safety or efficacy. Annual safety reviews, includes, but may not be limited to review of safety data, enrollment status, stopping rules if applicable, accrual, toxicities, reference literature, and interim analyses as provided by the sponsor-investigator. The SOC oversees the conduct of DUHS sponsor-investigator greater-than-minimal-risk intervention studies that do not have an external monitoring plan, ensuring subject safety and that the protocol is conducted, recorded and reported in accordance with the protocol, standing operating procedures (SOPs), Good Clinical Practice (GCP), and applicable regulatory requirements. The DCI Safety Oversight Committee (SOC) will perform annual reviews on findings from the DCI Monitoring Team visit and additional safety and toxicity data submitted by the Principal Investigator.

### **11.8 External Data and Safety Monitoring Board (DSMB)**

NIDA website describing the criteria for DSMB states “A Data and Safety Monitoring Board (DSMB) is generally required for Phase III clinical trials. For earlier medication trials (Phase I or II and some behavioral clinical trials), a DSMB may be appropriate if the study has multiple clinical sites, is blinded, tests a high-risk intervention, or is conducted in vulnerable populations.” According to these criteria, this study should not require a DSMB; it is not a Phase III clinical trial, does not use multiple clinical sites, is not blinded, does not test a high-risk intervention, and is not conducted in a vulnerable population.

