### 3 PROTOCOL SYNOPSIS AND RESEARCH SUMMARY

#### 3.1 Purpose

The purpose of this study is to assess an “adaptive” approach to smoking cessation pharmacotherapy. The protocol is designed to compare adaptive vs. standard approaches to two common smoking cessation pharmacotherapies (Varenicline and Nicotine Patch). The adaptive treatment approach provides the addition of Bupropion in the pre-quit period for participants who are not “responding” to initial treatment. Little is known about the adaptive use of Varenicline or Nicotine Patch, in which Bupropion is added to Varenicline or Patch for those who do not respond to one of these medications in a pre-quit treatment period. This study attempts to address these knowledge deficits. The study (N=300) is a double-blinded randomized placebo-controlled trial designed to compare biochemically-confirmed abstinence rates in smokers randomized to Varenicline Adaptive Protocol vs. Varenicline (N=150) and for comparison, Nicotine Patch Adaptive Protocol vs. Nicotine Patch (N=150). The “Varenicline Adaptive Protocol” is conducted by starting treatment with Varenicline 4 weeks prior to the quit day, then following each participant’s response to this pre-treatment medication. After 2 weeks, if the patient shows a reduction greater than 50% in cigarettes smoked per day then the patient is considered to be a “Varenicline responder” and is continued on Varenicline alone out to 12-weeks post quit day. If the patient does not spontaneously decrease smoking in the pre-quit period by more than 50% cigarettes per day, the patient is considered to be a “Varenicline non-responder” and Bupropion is added to the Varenicline. For comparison, an identical protocol is used with nicotine patch vs. nicotine patch adaptive treatment. The study uses only FDA-approved medications: Varenicline, Nicotine Patch, Bupropion, and placebo controls. To pattern clinical practice, participants will be able to choose whether they would like to use a patch or Varenicline-based treatment. After choosing, however, they will be randomized to adaptive vs. non-adaptive version of that treatment. Placebo medications are matched throughout the study. Participants will be blinded to all medications. All participants will receive behavioral treatment including a single 40-minute visit with a medical provider. The study is designed to provide researchers and clinicians with a better understanding of how to use adaptive pharmacotherapy protocols to improve smoking cessation rates.

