## 7 INVESTIGATIONAL PLAN

### 7.1 Study Design

This study is a double-blinded, randomized-controlled trial. Participants will be randomized to Varenicline- or Nicotine Patch-based adaptive pharmacotherapy algorithm or to standard treatment with Varenicline or the Nicotine patch.

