#### 7.1.5. Study Drug Blinding

Subjects are blinded to their active medications. Study personnel who are in contact with participants, including the CTA, study clinician, and PI, are blinded to active medication.

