## 10 TRIAL PROCEDURES AND ASSESSMENTS

### **Relationship of this study to the Duke Translational Smoking Cessation Program (TSCP) and Duke Center for Smoking Cessation (CSC)**

Study recruitment will take place among a clinical population via three routes - the TSCP Clinics, Duke Primary Care (DPC) Clinics, and the Center for Smoking Cessation (CSC).

**Duke Translational Smoking Cessation Program (TSCP):** Most patients in this study will be recruited through the Duke TSCP clinics – a network of six clinics throughout the Duke University Health System (DUHS) that receive roughly 250 patient referrals per month. The TSCP is a growing program expanding to serve patients across Duke Health. [name], the PI for this study, is Director of the TSCP and oversees all TSCP personnel and processes. Each TSCP Clinic site contains a provider trained in tobacco cessation treatment (typically an APP (Advanced Practice Provider)) who performs a thorough evaluation, conducts physical exams and prescribes medication and a Medical Assistant or Staff Assistant who assists with data collection. The TSCP is designed with a research infrastructure in which data is collected in a standardized format and research staff who recruit patients are present on site for studies. The TSCP contains centralized operations including a clinic coordinator who calls patients for scheduling and follow up. Every patient who is scheduled for an appointment at a clinic within the TSCP will be screened for research study eligibility. If a patient could potentially be eligible for a research study, a note will be made in their medical chart. Research staff will then attempt to reach out to them to see if they are interested in participating in a research study (via MyChart message and then via phone). If the patient is interested in the study and meets the inclusion criteria, the patient will be scheduled to meet research staff at the TSCP clinic or the CSC for a screening visit. If the potential participant is not interested in a research study or not eligible, a note will be made in their medical record and they will be encouraged to keep their regularly scheduled clinic visit.

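### Section 11.8 decides against a DSMB partly because the trial is said not to be blinded, but the trial is double-blind, and the protocol names no one to review safety by arm during treatment

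*Protocol*

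**What the plan says.** Section 11.8 cites the funder's criteria. A DSMB is generally required for Phase III trials; for earlier trials, "a DSMB may be appropriate if the study has multiple clinical sites, is blinded, tests a high-risk intervention, or is conducted in vulnerable populations". The section then argues that none is needed here: "it is not a Phase III clinical trial, does not use multiple clinical sites, is not blinded, does not test a high-risk intervention", and the population is not vulnerable.

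Other sections describe the design differently:

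- Section 3.1: the study "is a double-blinded randomized placebo-controlled trial designed to compare biochemically-confirmed abstinence rates".
- Section 7.1: "This study is a double-blinded, randomized-controlled trial".
- Section 7.1.5: subjects are blinded, and "Study personnel who are in contact with participants, including the CTA, study clinician, and PI, are blinded to active medication".
- Section 11.3: "All study staff in direct contact with participants will be blinded to the randomization to adaptive vs standard treatment algorithms". The Clinical Research Coordinator can see the allocation for emergency unblinding.

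Without a DSMB, oversight falls to the SOC (Section 11.7). It meets the data annually, through the findings of the Monitoring Team and "additional safety and toxicity data submitted by the Principal Investigator". Section 12.1 sets routine monitoring at 1 to 3 subjects a year after a first visit. The one planned interim analysis (Section 13, Interim Analyses) follows the 12-week visit of all 300 participants.

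**The concern.** The decision on independent oversight is argued from a list of facts, and one of them is the opposite of what the protocol says about its own design. This is more than a slip of wording, because blinding is one of the criteria that 11.8 cites and then applies. Whoever approved the monitoring arrangement on the strength of 11.8 was told that this criterion was not met.

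The fallback makes the point practical. The investigator who supplies safety data to the SOC is blinded, so on the route described those data arrive without arm. Exposure differs by arm, and a difference in harm between the arms can be seen only by someone who looks at them separately. The protocol does not say who that would be while participants are still on treatment.

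**Working it through.** The protocol gives no figure to reproduce here. The check is a comparison of sections, with some simple arithmetic on exposure.

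**1. The five grounds in 11.8 against the rest of the protocol.**

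| Ground in 11.8 | Rest of the protocol | Result |
|---|---|---|
| Not blinded | 3.1, 7.1, 7.1.5 and 11.3: double-blind, placebo-controlled; participants, clinical trials assistant (CTA), clinician and PI blinded | Contradicted |
| No multiple sites | Section 10: recruitment through six cessation clinics and three primary care clinics, with screening at a cessation clinic or the central center; 11.2.1 calls the institution the lead center. But all clinics belong to one health system, and Section 10 names a central study site | Unclear |
| Not Phase III, not high-risk, not vulnerable | Not examined here | Left as stated |

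**2. Who sees safety data, and in what form.**

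- SOC, from the PI: annual; the PI is blinded (7.1.5, 11.7).
- SOC, from the Monitoring Team: annual; 1 to 3 subjects of 300, that is 1/300 = 0.3% to 3/300 = 1.0% of the sample a year (12.1).
- IRB: an annual list of all AEs, with no mention of arm (11.1.2).
- Manufacturer, funder, IRB and FDA: individual SAE reports (11.2.1).
- Interim analysis: after the 12-week visit of all 300. Treatment runs to 12 weeks after the target quit day (TQD) (3.5), so by then everyone has finished treatment.

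None of these routes assigns anyone to tabulate or compare safety by randomized arm before treatment is over.

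**3. How exposure differs by arm (Section 10.2).** Active bupropion goes only to non-responders in the adaptive arms; responders and both standard arms receive placebo bupropion. With 75 adaptive participants in each drug choice, the expected number on active bupropion is 75 × (patch non-responder share) + 75 × (varenicline non-responder share).

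- Shares in the Sample Size Calculation (58.8% and 64.6%): 75 × 0.588 + 75 × 0.646 = 44.1 + 48.45 = 92.55, about 93 of 150 (62%).
- Share in Section 3.2 (50%): 75 × 0.50 + 75 × 0.50 = 75 of 150 (50%).
- Standard arms: 0 of 150.

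Timing differs too. The adaptive arms start active drug 4 weeks before the TQD. The varenicline standard arm starts 1 week before, and the patch standard arm on the day itself. Active treatment is therefore exclusive to the adaptive arms for 4 − 1 = 3 weeks with varenicline and for 4 weeks with patch.

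**The case against.** Several points on the other side stand.

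- The criterion cited in 11.8 says only that a DSMB may be appropriate, and three of the five grounds are not disputed. A reader might infer that correcting the blinding statement makes a DSMB compulsory. It does not; the decision could come out the same way.
- A reader might take the site ground to be contradicted as well. The documents do not go that far. Recruiting and screening clinics within one health system, with a named central site, can fairly be called a single site. The lead-center wording muddies this, and clarification is the most that can be asked.
- A reader might conclude that nobody reviews safety by arm, or that only pooled data ever reach a reviewer. That infers practice from silence. The coordinator holds the allocation, the statistician is not stated to be blinded, the Monitoring Team may ask for any study document, and nothing forbids a closed report. Section 14.6 also relies on an institutional monitoring plan that is not at hand, although it refers back to 11.7 and 11.8 for detail.
- Other safety routes exist: expedited individual SAE reports, causal attribution of each AE, emergency unblinding, and extra monitoring if toxicity is unexpectedly frequent. They can pick up a striking single case. None is described as a comparison between arms.
- Not all early active treatment is in the adaptive arms, since standard varenicline also starts before the TQD.

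One could try to defend the statement in 11.8 on the ground that staff know whether a participant chose varenicline or patch (11.3). But that choice is not randomized. The randomized comparison is adaptive against standard, and contact staff are blinded to it. Section 10.1 has the CTA pass randomization status to the pharmacy, which sits awkwardly with the blind but does not make the design open.

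**Conclusion.** The concern holds for the blinding ground, with high confidence: 11.8 says the reverse of four other sections, on a criterion it cites itself. The recorded reasoning for having no DSMB therefore fails on one of its five grounds and is unclear on a second. That calls for correction and a fresh decision, and does not by itself show that the outcome was wrong.

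On review by arm, the supportable statement is that the protocol names no one who prepares or reviews safety by arm before all 300 have finished treatment. The gap matters because about 75 to 93 of 150 adaptive participants would receive active bupropion against none of 150 in the standard arms, and because the adaptive arms alone receive active drug in the first 3 weeks (varenicline) or all 4 weeks (patch) before the TQD. Those counts assume 75 participants per arm as planned, no loss before the response visit, and one or other of the protocol's non-responder shares. The protocol gives no expected rate of serious events, so how large an excess might go unnoticed cannot be put in figures.

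**What to change.** 1. Correct the blinding statement in 11.8 so that it agrees with 3.1, 7.1, 7.1.5 and 11.3.
2. State whether the clinics in Section 10 count as one site or several, and bring the lead-center wording in 11.2.1 into line.
3. Re-take the DSMB decision on those facts and record the reasons. Keeping the SOC remains open.
4. If the SOC remains the reviewer, state in 11.7 that a role already holding the allocation (the coordinator with unblinding access, or the research pharmacy) gives it a closed table of AEs, SAEs and withdrawals by arm at each annual review, with the PI and contact staff kept blind.

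The cost is a few lines of protocol text and one table a year, which someone other than the PI must prepare. Sample size, treatment and the efficacy analysis are unaffected.

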## **12 QUALITY CONTROL AND QUALITY ASSURANCE**

### **12.1 Monitoring**

The Duke Cancer Institute (DCI) Monitoring Team will conduct monitoring visits to ensure subject safety and to ensure that the protocol is conducted, recorded, and reported in accordance with the protocol, standard operating procedures, good clinical practice, and applicable regulatory requirements. As specified in the DCI Data and Safety Monitoring Plan, the DCI Monitoring Team will conduct routine monitoring after the third subject is enrolled, followed by annual monitoring of 1 – 3 subjects until the study is closed to enrollment and subjects are no longer receiving study interventions that are more than minimal risk.

Additional monitoring may be prompted by findings from monitoring visits, unexpected frequency of serious and/or unexpected toxicities, or other concerns and may be initiated upon request of DUHS and DCI leadership, the DCI Cancer Protocol Committee, the Safety Oversight Committee (SOC), the sponsor, the Principal Investigator, or the IRB. All study documents must be made available upon request to the DCI Monitoring Team and other authorized regulatory authorities, including but not limited to the National Institute of Health, National Cancer Institute, and the FDA. Every reasonable effort will be made to maintain confidentiality during study monitoring.

### **12.2 Audits**

The Duke School of Medicine Clinical Trials Quality Assurance (CTQA) office may conduct confidential audits to evaluate compliance with the protocol and the principles of GCP. The PI agrees to allow the CTQA auditor(s) direct access to all relevant documents and to allocate his/her time and the time of the study team to the CTQA auditor(s) in order to discuss findings and any relevant issues.

CTQA audits are designed to protect the rights and well-being of human research subjects. CTQA audits may be routine or directed (for cause). Routine audits are selected based upon risk metrics generally geared towards high subject enrollment, studies with limited oversight or monitoring, Investigator initiated Investigational Drugs or Devices, federally-funded studies, high degree of risk (based upon adverse events, type of study, or vulnerable populations), Phase I studies, or studies that involve Medicare populations. Directed audits occur at the directive of the IRB or an authorized Institutional Official.

CTQA audits examine research studies/clinical trials methodology, processes and systems to assess whether the research is conducted according to the protocol approved by the DUHS IRB. The primary purpose of the audit/review is to verify that the standards for safety of human subjects in clinical trials and the quality of data produced by the clinical trial research are met. The audit/review will serve as a quality assurance measure, internal to the institution. Additional goals of such

audits are to detect both random and systemic errors occurring during the conduct of clinical research and to emphasize “best practices” in the research/clinical trials environment.

## **12.3 Data Management and Processing**

### **12.3.1. Case Report Forms (CRFs)**

The eCRF will be the primary data collection document for the study. The CRFs will be updated in a timely manner following acquisition of new source data. Only approved study staff, Principal Investigator, Study Coordinator, and Clinical Trials Assistants, are permitted to make entries or corrections in the CRF.

An audit trail will be maintained automatically by the electronic CRF management system in REDCap and Epic. Designated personnel will complete user training, as required or appropriate per regulations.

